In order to address the primary aim of the study to prove that treating patients without a tamponade dressing after hemorrhoidectomy results in a lower pain burden while the incidence of bleeding requiring surgical revision is no greater than in the patients treated with tamponade (non-inferiority), the primary outcome variables will be examined in terms of an a priori ordered hypothesis at a level of significance of 0.05. Pain values will be described by the mean (SD) and median (IQR). The last observation carried forward (LOCF) method will be used to replace missing values for pain, but only if at least one documentation of postoperative pain is available. Differences in pain will be analyzed using the non-parametric U test (two-sided; alpha = 0.05). If significantly lower pain levels are detected in the treatment arm without tamponade, non-inferiority in the bleeding rate will be also be analyzed at the 5% significance level. Alpha error correction is not required [27]. The incidence of postoperative bleeding needing revision (bleeding rate) will be determined in both treatment arms and will be tested for non-inferiority by calculating the 90% confidence interval (CI) (one-sided hypothesis), with a rate of bleeding two times higher considered acceptable, whereas a bleeding rate three times higher will no longer be considered non-inferior. This rate difference (together with the 90% CI margins) will be considered in relation to the observed revision rate in the control arm. This gives the estimator for the relative increase together with the confidence margins. If the upper limit of this relative increase exceeds 3, then a threefold increase is still possible and non-inferiority is rejected. If the upper limit of this relative increase is < 3, non-inferiority is assumed (with an error rate of 5%). In the unexpected case that the revision rate in the control group is rather low (< 2%) or even 0%, the relative increase will not be calculated. In this case, only the revision rates in the treatment groups are reported (with the 95% CI). The number of patients requiring tamponade in the postoperative course in the group that did not receive primary tamponade after surgery will be presented with the 95% CI.

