Based on the results of the single-center pilot study that demonstrated significant pain reduction (first primary outcome) without tamponade, it can be assumed with great probability that an advantage can also be demonstrated in this much larger multicenter study (first hypothesis). For the second primary outcome based on the results of the pilot study and the international literature it is predicted that 4% of the patients will need surgical revision with tamponade due to severe postoperative bleeding in the treatment group (96% estimated success rate in the control group).

In the intervention group without tamponade a slightly higher rate of bleeding needing surgical revision of ca. 8% is expected. The bleeding rate was 10% in 52 cases included in the pilot study. Therefore, the clinically acceptable and justified limit for non-inferiority is set at 12%, or 8% higher than in the control group with tamponade (8% non-inferiority limit).

Based on these assumptions, the sample size is 433 per group, or 866 patients in total. For study enrollment, assuming a maximum 10% rate of loss to follow up, 953 patients are required. The power was set at 80% in all calculations. Detailed procedures for executing the statistical analysis of the primary and secondary variables and other data will be provided in a statistical analysis plan.

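### The trial is sized for a fixed 8-point difference, but the decision divides the confidence limits by the observed control rate; the stated 5% error does not hold, and the 80% power belongs to a different test

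*Protocol article*

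**What the plan says.** Everything at issue stands in the protocol article, section Statistical analysis and power calculation.

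**Sample size.** For control, "it is predicted that 4% of the patients will need surgical revision with tamponade"; without tamponade, "a slightly higher rate of bleeding needing surgical revision of ca. 8% is expected". The "limit for non-inferiority is set at 12%, or 8% higher than in the control group with tamponade (8% non-inferiority limit"). Then: "Based on these assumptions, the sample size is 433 per group, or 866 patients in total", and "The power was set at 80% in all calculations". This is an absolute margin on the difference of two rates.

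**Decision.** Bleeding is the second step of an ordered test, after pain. It is "tested for non-inferiority by calculating the 90% confidence interval (CI) (one-sided hypothesis"). The difference and its limits are then related to the revision rate observed in the control arm, which yields a relative increase with limits. The rule is: "If the upper limit of this relative increase is < 3, non-inferiority is assumed (with an error rate of 5" per cent). The same paragraph describes a doubled rate as acceptable and a tripled rate as not.

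**Exception.** If "the revision rate in the control group is rather low (< 2%) or even 0%, the relative increase will not be calculated"; in that case only the two rates with 95% intervals are reported.

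**The concern.** The margin behind the sample size is fixed; the margin in the decision moves with the data. If the threshold means a threefold rate, the permitted difference is twice the observed control rate: 6 points at 3%, 8 at 4%, 10 at 5%. If it means difference over control rate below 3, the permitted difference is 9, 12 and 15 points. The two parts of the section agree only at a control rate of exactly 4%, and only on the threefold reading.

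Dividing the limits of a difference by an estimated rate does not give a 90% interval for the ratio. The control rate is estimated from about 433 × 0.04 ≈ 17 events, and its sampling error as a divisor is left out. The interval is too short, and the error favours declaring omission of the tamponade non-inferior for bleeding that needs reoperation. That verdict is one of the two primary results.

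**Working it through.** **Inputs (protocol article):** control 4%, intervention 8%, limit 12%, one-sided 5% through a 90% interval, power 80%, 1:1 allocation, 433 per group.

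**Assumptions:** Wald limits for the difference, because the article names no method; 433 evaluable patients per arm; the pain hypothesis has been met, so that the bleeding test is reached.

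**1. The plan's own figure.** For a fixed 8-point margin with unpooled variance:

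n = (1.645 + 0.8416)² × (0.04×0.96 + 0.08×0.92) / (0.08 − 0.04)² = 6.183 × 0.112 / 0.0016 = 432.8, so 433.

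The stated size is reproduced, but for the fixed difference test.

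**2. Exact behaviour of each rule.** Write c for the observed control rate and U for the upper 90% limit of the difference. Both binomials were enumerated in full at 433 per arm, with no claim allowed when c < 2%.

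| Rule | Accepts 8% vs 4% (power) | Accepts 12% vs 4% | Accepts 16% vs 4% |
|---|---|---|---|
| Fixed: U < 8 points (Wald) | 79.5% | 5.6% (error) | – |
| Threefold reading: 1 + U/c < 3 | 66.4% | 17.5% (error) | – |
| Literal reading: U/c < 3 | 91.7% | 59.0% | 21.2% (error) |

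On the threefold reading, the error at a true ratio of 3 is 17.4 to 17.6% for true control rates from 2% to 6%.

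**3. Why it happens, and why more patients do not help.** The threefold rule is equivalent to testing pT − 3pC < 0, but with the standard error of pT − pC. At 12% vs 4% the two variances, each times n, are:

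- used: 0.04×0.96 + 0.12×0.88 = 0.144
- needed: 9×0.04×0.96 + 0.12×0.88 = 0.4512

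The effective critical value is 1.645 × √(0.144/0.4512) = 0.929, a one-sided error of about 17.6%. The sample size cancels; exact enumeration at 1,200 per arm still gives 17.5%. The same step for the literal rule at 16% vs 4% uses 0.1728 and 0.7488: 1.645 × √(0.1728/0.7488) = 0.790, or about 21.5% (exact 21.2%).

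**4. Valid tests at 433 per arm.**

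- Difference scale, score-type (Farrington–Manning), limit 8 points: error 4.9% at 12% vs 4%, power 77.2% at 8% vs 4%.
- Ratio scale, limit 3, log rate ratio: error 5.4%, power 40.9%. For 80% power, n = 6.183 × (0.96/0.04 + 0.92/0.08) / (ln 3 − ln 2)² ≈ 1,335 per arm.
- Ratio scale, contrast pT − 3pC: error 3.7%, power 33.7%. For 80% power, n = 6.183 × (0.0736 + 9×0.0384) / 0.04² ≈ 1,620 per arm.

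**5. The below-2% exception.** It applies with 8 or fewer control events out of 433. The binomial probability is 0.9% at a true control rate of 4%, 9.7% at 3%, 24.5% at 2.5% and 50.0% at 2%. The rates other than 4% are assumed. The Background gives 2–6% for postoperative bleeding in general, not for bleeding that needs revision.

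**The case against.** **The analysis plan may settle it.** The article defers detailed procedures to a statistical analysis plan that is not shown, and the Wald interval is an assumption made here. That plan could name an interval that carries both arms' variance. This helps only a little: the article already fixes the statistic, the divisor, the threshold, the exception and the claimed error rate.

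**The power loss depends on the reading.** A reader might infer that the rule simply leaves the trial underpowered. The text does not support that. The threefold reading, at 66.4%, fits the description of a tripled rate as unacceptable and the 12% limit. The literal wording relates a difference to the control rate, and then power is 91.7%, because the limit is in effect a fourfold rate. What stands is that the 80% was calculated for neither.

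**The below-2% exception is cautious.** A reader might also count it among the causes of the excess error. It is not one: it can never produce a claim of non-inferiority, and at 8% vs 4% and 12% vs 4% the threefold rule gives the same 66.4% and 17.5% without it. The article calls the case unexpected and says in advance what will be reported. What stands is a possible gap in the second primary hypothesis if the true control rate is well below the planned 4%.

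**The fixed 8-point margin is not a neutral repair.** With the score test, a true threefold rate would pass about 33% of the time at 9% vs 3% and 87% at 6% vs 2%, against the protocol's own statement that a threefold rate is not acceptable. This stands, and it shapes the fix.

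**Conclusion.** The point holds and should be corrected before analysis. The stated 5% error is wrong on either reading: 17.5% (threefold) or 21.2% (literal), each at its own boundary with a 4% control rate. The 80% power belongs to a fixed-difference test that the decision rule does not use; under the rule it is 66.4% or 91.7%. These figures rest on Wald limits, 433 evaluable patients per arm and the bleeding test being reached. The mechanism does not depend on sample size.

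The below-2% exception is a secondary caveat. It matters little at the planned rate, and its larger effects rest on assumed control rates of 2–3%. The documents do not support the inference that it inflates error, nor that the trial is underpowered whichever way the rule is read.

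**What to change.** Reconcile the sample-size and decision paragraphs on one scale, with an interval valid for that scale and error and power restated to match.

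**(a) Difference scale.** Non-inferior if the upper limit of a score-type 90% interval for the rate difference is below 8 points, applied at every observed control rate. State error 4.9% and power 77.2% at 433 per arm (Wald: 5.6% and 79.5%). State also that below a 4% control rate this margin permits more than a threefold rate, with the pass probabilities given above, and report the rate ratio with its own interval.

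**(b) Ratio scale.** Non-inferior if the upper limit of a 90% interval for the rate ratio, carrying both arms' variance, is below 3. Define the quantity as the rate ratio. Restate power as about 34–41% at 433 per arm, and say how a low or zero control count is handled so that a decision rule remains.

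**Cost.** Neither option needs extra patients if the lower power is accepted; 80% power under (b) would take roughly 1,335 to 1,620 per arm. Either is an amendment to a primary criterion after recruitment has started in an unblinded trial, so it should be dated and justified without reference to accumulating bleeding data. The stated power becomes less favourable, slightly under (a) and markedly under (b).

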### Design

The NoTamp study is designed as a German national, multicenter, randomized controlled clinical non-inferiority trial. Participants are randomly allocated in a 1:1 ratio to each treatment group. Randomization will be stratified per study site. Allocation to treatment groups will be performed using a centralized web-based tool. Randomization is recommended to be performed at the earliest 12 h before the start of surgery. The patient will not be informed about the result of randomization before surgery. The duration of the clinical trial for each randomized patient is 7 days. There will be no blinding of participants, physicians, nurses or outcome assessors. No interim analysis is planned.

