### Primary and secondary outcomes

Primary outcomes of the NoTamp study are maximum postoperative pain, as measured by a numerical rating scale (NRS) at four time points within 48 h after the surgical procedure, and the occurrence of postoperative bleeding with the need for surgical revision within 7 days after hemorrhoidectomy. Postoperative pain is measured at rest within routine care at 6, 12, 24, and 48 h after the surgical procedure. The most severe pain within 48 h of the surgical procedure will be compared between the treatment groups.

As a secondary outcome, the postoperative pain at each predetermined evaluation time point (6, 12, 24, and 48 h and 7 days after surgery) will be compared between treatment groups. Additionally, the change in pain intensity from 6 h after the surgical procedure to 12, 24, and 48 h and day 7 after the procedure and the development of pain between 24 and 48 h will be compared between the intervention and control group. The number of patients in the group without primary tamponade who require tamponade dressings will also be documented.

Further secondary endpoints that will be compared between the treatment groups are the use of analgesics; the lowest hemoglobin documented in clinical routine within 7 days; quality of life using EuroQuol 5 dimensions (EQ. 5D) at screening, on discharge and on day 7 and patient satisfaction on day 7. Patient satisfaction will be measured using the key figures “subjective treatment errors”; “subjective treatment success”; the satisfaction index and the expectation fulfillment scale of the Cologne Patient Satisfaction Questionnaire of Pfaff et al. [26].

For safety analysis all expected and unexpected AEs and SAEs occurring in temporal relation to the clinical trial will be documented and compared between the treatment groups. Documentation includes the causal relationship with the therapy to be investigated and/or with the previous surgical treatment. The nature of the event and the onset, end, and severity (mild, moderate, severe) of each AE will be documented. A full overview of the visit plan and the schedule of enrollment, interventions, and assessments are provided in Figs. 2 and 3.

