### Statistical analysis and power calculation

The analysis of the primary and secondary endpoints will be performed according to an adapted intention-to-treat (ITT) principle. There will be no interim analysis. The ITT analysis population will include all randomized participants who have undergone the surgical procedure (hemorrhoidectomy). The ITT analysis population will comprise participants assigned to the treatment group based on the randomization schedule, regardless of the treatment actually received. Randomization will be performed up to 12 h prior to the surgical intervention. However, without the surgical intervention there will be no postoperative wound that requires further treatment and thus there will be no data collected and analysis will not be possible. The study participant will therefore be excluded from the clinical trial if the scheduled surgery is not performed. Patients who are excluded from the trial after randomization and before the start of the observation period (postoperative wound care with or without tamponade) are replaced by another study participant in order to achieve the required number of cases. The randomization sequence will be continued. The next patient does not receive the randomized allocation of the excluded patient. The study will be continued until the required number of evaluable patients has been reached. Due to complications it may not be possible to comply with the randomly assigned treatment regimen in a very small number of patients. These patients will not be excluded from the study. Study participants will also be excluded from the clinical trial if a surgical procedure other than Milligan-Morgan or Parks is performed, which does not result in an open wound.

Details of participants’ baseline characteristics including preoperative pain and hemoglobin levels will be provided, but the data will not be compared statistically (by calculating the *p* value) because any differences between groups at this point must arise by chance (if randomized properly).

As a secondary approach, a per-protocol (PP) analysis will be performed excluding patients with any serious protocol deviations, if applicable. The safety analysis will be performed based on the as-treated (AS) population.

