Pain values at all predetermined survey times and the development of pain between selected time points will be compared in the two treatment groups using the U test. The lowest hemoglobin values in the postoperative period up to day 7 will be compared in the two treatment groups using the two-sided *t* test. The amount and type of postoperative pain medication will be described by percent values for each treatment group. For the safety analysis the incidence of AEs and SAEs by category (severity) will be compared in the two treatment groups using Fisher’s exact test.

There will be no a priori planned subgroup analysis, but a multivariate analysis of all study patients (ITT population) will be performed investigating the occurrence of severe postoperative bleeding (dependent variable). In this logistic regression, the following variables are considered as possible predictors (independent variables): age, gender, surgical method used (Milligan-Morgan or Parks), severity of hemorrhoids (grade III/IV), use of tamponade (yes/no), type of tamponade used, type of anesthesia used, occurrence of intraoperative complications, preoperative hemoglobin levels, type and amount of pain therapy (in particular the performance of a pudendal block), and type and amount of anticoagulation therapy. If this multivariate analysis shows that there is a significant predictor of bleeding that is not evenly distributed within the two study groups (significance in demonstrating the comparability of the two groups), a subgroup analysis of this variable will be performed. In this case, primary and secondary endpoints will be analyzed as described previously, in the subgroups of the unequally distributed variable.

Mental illness in the study participants, preoperative pain levels, the use and type of concomitant pain therapy, and the type of tamponade used represent factors possibly influencing pain, quality of life, and patient satisfaction. The influence of these factors on the aforementioned outcomes will be examined.

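### The named treatment comparisons use neither the site strata nor the preoperative values, which costs precision, and pain change is measured from a 6 h reading taken after treatment began

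*Protocol article*

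**What the plan says.** Under Design, the protocol article states "Randomization will be stratified per study site" and "Participants are randomly allocated in a 1:1 ratio to each treatment group". The treatment comparisons are named under Statistical analysis and power calculation:

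- **Maximum pain (first primary outcome):** "Differences in pain will be analyzed using the non-parametric U test (two-sided; alpha = 0.05").
- **Bleeding needing revision (second primary outcome):** it "will be tested for non-inferiority by calculating the 90% confidence interval (CI) (one-sided hypothesis").
- **Secondary pain outcomes, likewise by U test:** "Pain values at all predetermined survey times and the development of pain between selected time points will be compared in the two treatment groups using" that method.
- **Hemoglobin:** "The lowest hemoglobin values in the postoperative period up to day 7 will be compared in the two treatment groups" by a two-sided t test.

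None of these names site or a preoperative value. Yet the same section says that "baseline characteristics including preoperative pain and hemoglobin levels will be provided", so the values are collected. Preoperative hemoglobin appears again only as a candidate predictor in the logistic regression of severe bleeding, a list that omits site. Preoperative pain appears only among factors whose influence on pain, quality of life and satisfaction will be examined by an unstated method.

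Under Primary and secondary outcomes, the secondary pain outcomes include "the change in pain intensity from 6 h after the surgical procedure to 12, 24, and 48 h and day 7 after the procedure". Under Intervention and comparison, the tamponade is placed during the operation and usually stays no longer than 24 h.

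**The concern.** Three features of the plan do not fit together.

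1. Site is a design factor, and it may well be prognostic: Setting and Previous and concomitant medication and therapy leave analgesia and other care to local practice, and Intervention and comparison leaves the type of tamponade to routine. When arms are balanced within sites, a test that ignores site keeps the between-site variation in its error term.
2. Aim of the study sets a comparison involving both preoperative and postoperative hemoglobin, but the test uses only the lowest postoperative value. A preoperative measurement that could sharpen the comparison is left out of it.
3. A change score is a clean treatment contrast only if its starting value precedes treatment. The 6 h reading does not. If tamponade hurts while in place, as the trial hypothesises, that arm starts higher and has further to fall.

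The first two points cost precision. The third affects what a secondary result means, and possibly its direction.

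**Working it through.** **The plan's own figure.** The only sample size given is for bleeding. With success rates of 96% and 92%, a margin of 8 points, one-sided 5% and 80% power:

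n = (1.645 + 0.842)² × (0.96×0.04 + 0.92×0.08) / (0.08 − 0.04)² = 6.183 × 0.112 / 0.0016 = 433 per group.

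This matches the protocol, and nothing below changes it.

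**Site and the pain test.** The documents give neither an intraclass correlation (ICC) nor a number of sites, so both are assumed. The simulation used 20 sites of 44 patients with arms balanced 22:22 in each, and a 0–10 scale rounded and truncated from a latent SD of 2.5. There were 6,000 runs under no effect and 2,000 with a 0.5-point shift.

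| Assumed ICC | Type I error, U test | Type I error, van Elteren | Power, U test | Power, van Elteren |
|---|---|---|---|---|
| 0 | 4.9% | 5.0% | 82% | 82% |
| 0.05 | 4.5% | 5.0% | 82% | 84% |
| 0.10 | 4.0% | 4.8% | 83% | 85% |
| 0.20 | 3.2% | 5.2% | 85% | 89% |

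A large-sample check, 2(1 − Φ(1.96/√(1 − ICC))), gives 4.4%, 3.9% and 2.8% at ICC 0.05, 0.10 and 0.20, in the same direction. Exact balance within sites is itself an assumption; looser balance would make the plain test less conservative.

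**Hemoglobin.** With correlation ρ between preoperative and lowest postoperative value (assumed), ANCOVA leaves a fraction 1 − ρ² of the variance. Power for an assumed difference of 0.15 SD at 433 per group is Φ(0.15 × √(433/2) / √(1 − ρ²) − 1.96).

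| ρ | Variance left | Variance removed | Power |
|---|---|---|---|
| unadjusted | 1.00 | – | 60% |
| 0.3 | 0.91 | 9% | 64% |
| 0.5 | 0.75 | 25% | 72% |
| 0.7 | 0.51 | 49% | 87% |
| 0.8 | 0.36 | 64% | 96% |

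**Change from 6 h.** Let D(t) be mean pain without tamponade minus mean pain with it at time t; negative values favour no tamponade. The between-arm difference in change is D(t) − D(6 h).

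- Constant 1-point benefit: −1 − (−1) = 0. The benefit disappears from view.
- A 1-point benefit at 6 h that has gone by 48 h: 0 − (−1) = +1, apparently favouring tamponade.
- Illustrative means falling from 6 to 3 with tamponade and from 4 to 2 without: changes of −3 and −2, so the arm with more pain at both times shows the larger improvement.

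**Bleeding.** At the planned rates, 433 × 0.04 + 433 × 0.08 gives about 52 events. If site rates had an SD of 3 points around 6% (assumed), ICC = 0.03² / (0.06 × 0.94) = 0.016, and ignoring site inflates the standard error by 1/√(1 − 0.016) − 1, about 0.8%.

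**The case against.** The strongest reply is that the protocol defers detailed procedures to a statistical analysis plan, which is not shown and could add strata and covariates. That is possible. But the protocol goes beyond deferral and names each test, and a plan that follows those names as they stand would be unstratified and unadjusted.

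Several other objections stand and limit the point:

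- A reader might infer that preoperative data are ignored altogether. They are not: both measurements enter supplementary analyses, and Setting and Discussion promise to evaluate local standards and concomitant therapy. None of these is specified as an adjustment of the pain or hemoglobin comparison.
- A reader might infer that the unstratified tests are biased or too liberal. They are valid, and conservative if site matters.
- The pain result is unlikely to turn on this. The pilot gave p = 0.001 with 100 patients, z of about 3.3. If that effect held, 866 patients would give 3.3 × √8.66, about 9.7; half the effect would give about 4.8.
- Saying that most of the hemoglobin precision is lost would need ρ² above 0.5, so ρ above about 0.71, which the documents do not supply.
- The hemoglobin aim could mean comparing arms on each value separately, which makes the mismatch with the test less certain.
- Change from 6 h is secondary, and the protocol does not call 6 h a baseline. Pain is also compared directly at 6, 12, 24 and 48 h and day 7, where a reversal like the one above would be seen.

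**Conclusion.** The point holds as one about efficiency and interpretation. The named comparisons leave out the stratification factor, and those for pain and hemoglobin leave out the preoperative value of the outcome. For pain, the cost is a type I error of about 4.9–3.2% instead of 5% and about 0–4 points of power, over assumed ICCs of 0–0.20. For hemoglobin it is 9–64% of the variance, over assumed correlations of 0.3–0.8. Site number, ICC, within-site balance and correlation are all assumptions. No material gain from stratifying the bleeding interval has been shown.

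The 6 h change can mislead without any assumption about ICC or correlation, because its reference follows the start of treatment. The documents do not support the further inference that either primary conclusion is biased or endangered.

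**What to change.** - **Maximum pain:** replace the plain U test with its site-stratified form (van Elteren), with a rule set in advance for pooling small sites.
- **Lowest hemoglobin:** replace the t test with ANCOVA on arm, site and preoperative hemoglobin. This also brings the test into line with the stated aim.
- **Pain course:** rely on the between-arm comparisons already planned at each time point, optionally in one longitudinal model adjusted for preoperative pain. Drop change from 6 h as a between-arm efficacy comparison, or label it descriptive.
- **Bleeding:** stratifying the interval by site is optional, with little gain expected. If done, it must fit the protocol's decision rule, which sets the upper limit of the relative increase against 3; a stratified interval for the difference alone would bypass that rule.

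The cost is wording, slightly more analysis work and the pooling of small sites. The data are already to be collected and the sample size is unaffected.
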